## Abstract

**Background:**

Postoperative nausea and vomiting is one of the most common complications affecting patients after surgery and causes significant morbidity and increased length of hospital stay. It is accepted that patients undergoing surgery on the bowel are at a higher risk. In the current era of minimally invasive colorectal surgery combined with enhanced recovery, reducing the incidence and severity of postoperative nausea and vomiting is particularly important. Dexamethasone is widely, but not universally used. It is known to improve appetite and gastric emptying, thus reduce vomiting. However, this benefit is not established in patients undergoing bowel surgery, and dexamethasone has possible side effects such as increased risk of wound infection and anastomotic leak that could adversely affect recovery.

**Design:**

DREAMS is a phase III, double-blind, multicenter, randomized controlled trial with the primary objective of determining if preoperative dexamethasone reduces postoperative nausea and vomiting in patients undergoing elective gastrointestinal resections. DREAMS aims to randomize 1,350 patients over 2.5 years.

Patients undergoing laparoscopic or open colorectal resections for malignant or benign pathology are randomized between 8 mg intravenous dexamethasone and control (no dexamethasone). All patients are given one additional antiemetic at the time of induction, prior to randomization. Both the patient and their surgeon are blinded as to the treatment arm.

Secondary objectives of the DREAMS trial are to determine whether there are other measurable benefits during recovery from surgery with the use of dexamethasone, including quicker return to oral diet and reduced length of stay. Health-related quality of life, fatigue and risks of infections will be investigated.

**Trial registration:**

ISRCTN21973627

## Background

Postoperative nausea and vomiting (PONV) is one of the most common complications affecting patients after surgery. The pathophysiology of PONV is multifactorial, but as patients undergoing colorectal surgery are exposed to various causative agents in addition to the physical factors of bowel manipulation predisposing to ileus, they are at a substantially higher risk of this problem. Following surgical intervention, patients view PONV as a very undesirable outcome, even more unpleasant than pain [1]. It causes significant morbidity, delays nutrition and increases the length of stay in hospital. Given that over 60,000 colorectal operations are performed annually in the UK alone, PONV has significant medical and cost implications to healthcare.

### Pathophysiology of PONV

The pathophysiology of nausea and vomiting is complex. The vomiting centre in the medulla receives stimulation from various sources, including the chemoreceptor trigger zone, enteric vagal nerve afferents, the vestibular system and the cerebral cortex. The multifactorial mechanisms underlying PONV include stimulation of dopamine and 5-hydroxytryptamine type 3 receptors in the chemoreceptor trigger zone by noxious substances such as opiates and anaesthetic agents, and the stimulation of gut chemoreceptors and stretch receptors. Despite advances in antiemetic agents, anaesthetic agents and minimally invasive surgical techniques, PONV remains a significant and persistent problem. Other risk factors that increase the likelihood of PONV are female gender, non-smoking status, history of motion sickness, childhood and young adulthood, and increasing length of surgery [2]. Intra-abdominal and laparoscopic surgery has been implicated as having an increased risk of PONV. A comparison of predictive models for PONV [3] found that intra-abdominal surgery had an odds ratio of 1.23 (n = 217) but this included patients who underwent gynecological laparoscopy. Laparoscopic cholecystectomy had an odds ratio of 2.85 (n = 42).

### Clinical relevance of PONV

After surgery, the overall incidence of PONV is 30%, and it is up to 70% in high-risk patients [2]. In a study investigating the 10 most undesirable postoperative outcomes, vomiting ranked first, gagging on the endotracheal tube second, and postoperative pain third [1]. Nausea was ranked fourth. Although mortality rates are rarely affected, PONV can cause significant morbidity including dehydration, electrolyte disturbance, delayed return to diet and aspiration pneumonia. Delayed recovery in the hospital setting predisposes to serious and life-threatening complications such as hospital-acquired pneumonia and thromboembolic events (deep venous thrombosis and pulmonary embolism). The delay in patients resuming an oral diet affects nutrition and subsequent general well-being, predisposing to tissue breakdown, pressure sores, wound infection, fatigue, weakness and delay in mobilization.

In the current era of minimally invasive colorectal surgery combined with enhanced recovery protocols to optimize recovery and reduce the length of patient hospital stay, reducing the incidence and severity of PONV is particularly important. The cost implications related to prolonged hospital stay and the additional costs of further complications affect both open and laparoscopic surgery.

### Dexamethasone for PONV

Dexamethasone is extensively used in all types of surgery to reduce PONV (Table 1). In practice, dexamethasone is less widely used for control of PONV by anesthetists in gastrointestinal patients, perhaps because of a lack of proven efficacy in these patients. However, its use is advocated in some enhanced recovery programs (ERAS) to improve recovery after colorectal surgery [4-6].

**Table 1 T1:** Literature review of use of dexamethasone for PONV

**Author**	**Year**	**n**	**Type of surgery**	**Findings**	**Reference**
Apfel *et al.*	2004	5,199	Gynecological, Trauma, Abdominal, Otolaryngology	Ondansetron, dexamethasone, and droperidol each reduced the risk of PONV by 26%	[7]
Wallenborn *et al.*	2006	3,140	Gynecological, Trauma Abdominal, Otolaryngology	Metoclopramide plus dexamethasone is an effective, safe and cheap way to prevent PONV	[8]
Zagar-Shostari *et al.*	2009	60	Colorectal	Dexamethasone in an enhanced recovery protocol gives a significant reduction in early postoperative fatigue, and an attenuated peritoneal cytokine response	[9]
Kirdak *et al.*	2008	30	Colorectal	Dexamethasone has no significant effect on reducing postoperative pain, inflammatory response or PONV	[10]
Weren and Demeere	2008	118	Abdominal and Gynecological	Steroids are mostly effective in the prevention of late PONV (rather than early).	[11]
Hans *et al.*	2006	32	Abdominal	After dexamethasone, blood glucose levels increase in both patients without diabetes and those with type 2 diabetes undergoing abdominal surgery. In patients without diabetes blood sugar levels rose to a maximum of 10 mmol / litre	[12]
Coloma *et al.*	2001	80	Anorectal	Reduction in time to ‘home readiness’ in ambulatory surgery	[13]
Gautam *et al.*	2008	150	Laparoscopic cholecystectomy	Combination of ondansetron and dexamethasone is better than each drug alone	[14]
Tiippana *et al.*	2008	160	Laparoscopic cholecystectomy	Dexamethasone decreased the need for opiates	[15]
Bianchin *et al.*	2007	80	Laparoscopic cholecystectomy	Reduced PONV. No change in pain or time to discharge.	[16]
Wang *et al.*	1999	90	Laparoscopic cholecystectomy	Dexamethasone significantly decreased the incidence of PONV	[17]
Sanchez- Rodriguez *et al.*	2010	210	Laparoscopic cholecystectomy	Dexamethasone significantly reduced PONV at 0, 6, 12 hours and reduced postoperative pain and fatigue	[18]
Mathiesen *et al.*	2009	116	Gynecological	Reduced PONV. Combinations of paracetamol, pregabalin and dexamethasone did not reduce morphine consumption.	[19]
Biswas *et al.*	2003	160	Gynecological	Ondansetron plus dexamethasone is most effective in preventing PONV. Results comparable for single agents.	[20]
Yursek *et al.*	2003	60	Gynecological	Ondansetron, but not dexamethasone, prevented PONV by 3 h post operation	[21]
Wang *et al.*	2000	90	Gynecological	Dexamethasone significantly decreases the incidence of PONV	[22]
McKean *et al.*	2006	72	Otolaryngology	Significant decrease in PONV and pain scores	[23]
Mathew *et al.*	2004	210	Pediatrics	Dexamethasone is effective for the prevention of PONV after strabismus repair in children	[24]

PONV:postoperative nausea and vomiting.

Its precise mechanism of action is unknown but it has been proposed that the antiemetic properties arise due to activation of glucocorticoid receptors in the medulla [25], or by inhibiting central production of prostaglandins or inhibiting the release of endogenous opioids [26]. It is also known to improve appetite [27], and in combination with reduced nausea and vomiting, aids early recovery. Glucocorticoids can also reduce pain by suppression of bradykinin and neuropeptides from nerve endings [26].

Dexamethasone does have potential theoretical side effects such as increased risks of wound infections and anastomotic leaks that could adversely affect recovery, but a systematic review of 51 studies using a single dose of methylprednisolone in cardiac, general and trauma surgical patients found no significant increase in adverse events [28].

### Dexamethasone use in abdominal surgery

In 2008, a systematic review and meta-analysis of 17 randomized clinical trials looking at preoperative dexamethasone in patients undergoing laparoscopic cholecystectomy was published [29]. This review suggested that, regardless of co-intervention (the administration of other antiemetics in the control arm), dexamethasone reduced the incidence of nausea and vomiting. Small studies investigating use of dexamethasone to reduce PONV in many other fields of surgery have been undertaken (Table 1). However, there are only two single center colorectal trials, totaling 100 patients, that have assessed this guidance in patients undergoing gastrointestinal surgery [9,10]. Interestingly, one of these trials [9] measured cytokine levels in peritoneal drain fluid following colorectal surgery and found significantly reduced levels of IL-6, a pro-inflammatory cytokine produced by T-cells and macrophages. There was a significant reduction in IL-13 (a cytokine involved in type 2 T-helper cell responses), which is a stimulator of inflammation and tissue remodeling at sites of T-helper type 2 inflammation. There was also a reduction in plasma levels of IL-6 and IL-8, another major stimulator of the inflammatory response. These changes in cytokine levels correlated with improved fatigue scores.

The well-conducted Apfel *et al*. study from 2004 randomized over 4,000 patients and assessed 64 different combinations of anesthetic measures [7]. They concluded that dexamethasone was effective in preventing PONV. However, only 11% of patients in this study underwent general surgical procedures and only a small fraction of these underwent major colorectal surgery. Patients undergoing colorectal surgery comprise an especially high-risk population for PONV, and may gain considerable benefit from dexamethasone. As yet, there is little evidence to support its use in colorectal surgery and a prospective multicenter trial is required.

Apfel *et al*. also demonstrated that the type of volatile anesthetic used had no effect on the incidence of nausea and vomiting. The additional antiemetic given at induction will not be standardized in the proposed trial. This will maximize the generalizability of the findings.

### The need for DREAMS – a large, multicenter, randomized trial

Randomized controlled trials have shown a reduction in PONV among patients undergoing various other types of surgery who are given dexamethasone. In the absence of good evidence, dexamethasone is variably used in patients undergoing colorectal surgery. We have surveyed six major colorectal units in the West Midlands region and found that 25% of colorectal patients currently receive dexamethasone. The Dexamethasone Reduces Emesis After Major Gastrointestinal Surgery (DREAMS) trial seeks to determine the effectiveness of dexamethasone for colorectal patients. No adequately powered multicenter trial has been undertaken to conclusively assess the effect of dexamethasone on PONV in patients undergoing bowel surgery. The aim of DREAMS is to evaluate the potential benefits of a single dose of dexamethasone at induction for patients undergoing colorectal surgery. The findings from DREAMS may also give an indication of its appropriate use inside and outside of ERAS, although this would require further confirmatory research.

## Methods

### Trial design

The DREAMS trial is a two stage trial, comprising a pilot study followed by a large, phase III double-blind, multicenter, randomized controlled trial comparing the effects of a single dose of 8 mg intravenous dexamethasone on patient recovery after major gastrointestinal surgery. Centers in the UK undertaking major elective gastrointestinal surgery will be eligible to take part.

### Ethical approval

Full ethical approval has been gained from the East Midlands Research Ethics Committee (ref: 10/H0402/77).

### Randomized comparison

Patients undergoing laparoscopic or open gastrointestinal resections will be randomized, in a 1:1 ratio, between 8 mg intravenous dexamethasone and control. All patients must be given one additional antiemetic prior to randomization; however, this must not be dexamethasone.

### Inclusion criteria

All patients undergoing elective open and laparoscopic small and large bowel operations for malignant or benign pathology will be eligible for inclusion. This includes small and large bowel resections, defunctioning stomas and closures of stomas.

### Exclusion criteria

The exclusion criteria are:

•diabetes or hyperglycemia

•active gastric ulceration confirmed endoscopically

•acute angle glaucoma

•bowel obstruction

•pregnancy

•under 18 years of age

•patients currently taking any form of steroid medication, or have taken steroids in the last 3 months (except steroidal inhalers, suppositories, pessaries, eye-drops, one-off local injections to a joint and topical preparations)

•a known adverse reaction to dexamethasone

•patients taking immunosuppressive agents including, but not limited to, methotrexate and antiretrovirals.

On admission, patients will have blood glucose levels checked to exclude undiagnosed hyperglycemia. Patients unable or unwilling to give written informed consent for the study are also excluded.

### Primary outcome measure

The primary objective of the main phase of DREAMS will be to determine whether preoperative dexamethasone reduces PONV within the first 24 hours in patients undergoing elective gastrointestinal resections. The primary outcome measure will be the number of episodes of vomiting within 24 hours post-surgery, recorded prospectively on trial care charts.

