### Power calculation

The DREAMS trial aims to recruit a total of 1,350 patients from around 30 colorectal units. With 1,350 patients randomized, DREAMS would have 90% power to detect a 24% proportional reduction (37% to 28%) in episodes of PONV in patients taking dexamethasone after undergoing gastrointestinal surgery. This number includes an additional 10% for crossover and dropout. Subgroup analyses will be undertaken for variables for which the randomization is stratified (for example, enhanced versus non-enhanced recovery pathway, PCA versus epidural) using standard tests for interactions. Additional exploratory analyses will also be undertaken to investigate, for example, any correlation between operative length and risk of nausea and vomiting. Analysis of the study will be on an intention-to-treat basis.

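### The objective and the power statement name PONV but the primary outcome counts vomiting episodes, so the stated 90% power is not shown to apply to that outcome and the primary result alone supports a claim about vomiting only

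*Protocol article*

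**What the plan says.** Three statements bear on the point.

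- **Objective** (Primary outcome measure): the main phase is to "determine whether preoperative dexamethasone reduces PONV within the first 24 hours in patients undergoing elective gastrointestinal resections". The Abstract gives the same aim in terms of nausea and vomiting. The article expands PONV as postoperative nausea and vomiting.
- **Primary outcome** (same section, next sentence): "The primary outcome measure will be the number of episodes of vomiting within 24 hours post-surgery, recorded prospectively on trial care charts". This is a count, and nausea is not part of it.
- **Planning figures** (Power calculation): "90% power to detect a 24% proportional reduction (37% to 28%) in episodes of PONV in patients taking dexamethasone", with 1,350 patients in total. On losses: "This number includes an additional 10% for crossover and dropout".

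Nausea appears under Secondary outcome measure, through the PONV Intensity Scale and, together with vomiting, through the frequency of as-required antiemetic use. For background rates, Clinical relevance of PONV says: "After surgery, the overall incidence of PONV is 30%, and it is up to 70% in high-risk patients". The section on dexamethasone in abdominal surgery describes colorectal patients as at especially high risk. The article gives no rate for vomiting alone.

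**The concern.** The objective and the power statement name one event and the primary outcome measures another. Two things follow.

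The first is interpretation. A patient with severe nausea who never vomits adds nothing to the primary outcome. A positive primary result would show an effect on vomiting. Reporting it as a reduction in PONV, which is how the objective is worded, would go beyond what was measured.

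The second is power. Everyone who vomits has PONV, but not everyone with PONV vomits. In the same patients and over the same period, the proportion vomiting therefore cannot exceed the proportion with PONV. If 37% really is a composite rate, the vomiting rate in these controls is 37% or less, and the same proportional reduction is a smaller absolute difference. There is also a mismatch of scale. A fall from 37% to 28% describes proportions of patients, whereas the outcome is a number of episodes per patient, and a calculation for one does not give the power for the other.

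**Working it through.** **Inputs from the article.** Control rate 37%, treated rate 28%, power 90%, total 1,350, 10% for crossover and dropout (all Power calculation); 1:1 allocation (Randomization).

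**Assumptions.** Two-sided alpha of 0.05, which the article does not state, and any control rate other than 37%.

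**Step 1: does 1,350 follow from 37% and 28%?** For two proportions with pooled variance under the null and p̄ = (p1 + p2)/2,

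n per arm = [1.960·√(2p̄(1−p̄)) + 1.282·√(p1(1−p1) + p2(1−p2))]² / (p1 − p2)²

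With p1 = 0.37, p2 = 0.28 and p̄ = 0.325, the two square roots are 0.6624 and 0.6593, so n = 568 per arm.

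| Version | Per arm | Total | Total ÷ 0.9 |
|---|---|---|---|
| 37% vs 28%, no continuity correction | 568 | 1,136 | 1,263 |
| 37% vs 28%, continuity correction | 590 | 1,180 | 1,312 |
| Exact 24% reduction (37% vs 28.12%), continuity correction | 606 | 1,212 | 1,347 |

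The stated 1,350 is matched by the two versions with a continuity correction. One-sided versions give 1,027 and 1,076 and do not match. The arithmetic is therefore sound as a comparison of proportions of patients. It is not a calculation for a count of episodes.

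**Step 2: what if the proportion of controls who vomit is not 37%?** Keep the planned ratio (p2 = p1 × 28/37, a 24.3% reduction) and take 1,350 × 0.9 = 1,215 evaluable patients, about 607 per arm. Then

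power = Φ{ [(p1 − p2)·√n − 1.960·√(2p̄(1−p̄))] / √(p1(1−p1) + p2(1−p2)) }

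At 37% vs 28%: (0.09 × √607.5 − 1.960 × 0.6624)/0.6593 = (2.218 − 1.298)/0.6593 = 1.395, so power is 91.9%.

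At 30% vs 22.7%: (1.799 − 1.960 × 0.6230)/0.6209 = 0.930, so power is 82.4%.

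| Control rate (all but 37% assumed) | Treated rate | Power, 1,215 evaluable | N for 90% after 10% loss, no continuity correction |
|---|---|---|---|
| 45% | 34.1% | 97.5% | 929 |
| 37% | 28.0% | 91.9% | 1,263 |
| 33% | 25.0% | 87% | not computed |
| 30% | 22.7% | 82% | 1,698 |
| 25% | 18.9% | 73% | 2,160 |
| 20% | 15.1% | 61% | 2,854 |

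The last column should be compared with 1,263, the figure that the same formula gives at 37%, and not with 1,350. On this formula power passes below 90% somewhere between control rates of 37% and 33%.

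**Step 3: can the article settle which event the 37% describes?** It is labelled PONV. It lies a little above the overall PONV figure of 30% and well below the upper figure of 70% for high-risk patients, the group in which the article places colorectal patients. The label points to a composite rate and the level is compatible with a vomiting rate. Neither is conclusive.

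**The case against.** The strongest reply is that 37% may already be a vomiting rate, loosely labelled. It is low for composite PONV in patients described as especially high-risk, the trial's full name refers to emesis, and on this reading 1,350 is right and one word needs changing. The article condenses a full protocol that may give the source of the 37%, so the missing source is not a fault in itself. This part stands: the power loss is conditional, and if the true PONV rate were nearer 70%, vomiting could exceed 37% and power would be higher than planned.

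A second reply is that a broad objective measured by a narrower, chart-recorded outcome is a common and defensible choice. Vomiting is a component of PONV, and the article cites a study that ranks it the most undesirable postoperative outcome, with nausea fourth. This stands too. A reader might infer that the trial cannot answer its objective at all, and the document does not support that: the nausea scale and antiemetic use are collected as secondary outcomes on days 1, 3 and 5 (or day of discharge). A reader might also infer that the planning rate is known to belong to a different event and that the trial is underpowered. Nothing in the article establishes either.

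Neither reply removes the disagreement between statements that the article does make. Objective, outcome and power paragraph use two events and two scales, and at least one of them has to change under either reading of the 37%.

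**Conclusion.** The mismatch is established from the text. The objective and the power statement say PONV, the primary outcome is vomiting episodes, and the primary result alone can carry a claim about vomiting only. It is also established that 37% and 28% work as proportions of patients (1,312 to 1,347 recovered against 1,350), so the stated 90% power has not been shown to hold for a vomiting count or for a vomiting proportion.

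The size of any power loss is open. If 37% is the proportion of controls who vomit, power is about 92% with 1,215 evaluable patients and nothing is lost. If 37% is composite and vomiting is less common, power is 87%, 82%, 73% or 61% at assumed rates of 33%, 30%, 25% or 20%. At 45% it would be 97.5%. All these figures assume a two-sided 0.05 test, an unchanged 28/37 ratio and a binary endpoint. No fault was found in the sample-size arithmetic itself.

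**What to change.** 1. State the primary objective as reducing postoperative vomiting within 24 hours of surgery.
2. Put the endpoint and the power calculation on one scale. Either define the primary endpoint as the proportion of patients with at least one episode of vomiting within 24 hours, or keep the count and redo the calculation for a count.
3. Say which event the 37% describes. If it is vomiting, relabel it. If it is composite PONV, restate the power at the expected vomiting rate.
4. Confine claims about nausea, or about PONV as a whole, to the secondary outcomes.

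The cost is small: a narrower headline claim and possibly a less favourable stated power. No new data are needed. The trial was still recruiting at submission, with 719 patients entered, so the wording can be settled before the analysis.

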### Randomization

Secure internet-based central randomization is available 24 hours a day and will ensure concealment of treatment allocation. Each center and each randomizer will be provided with a unique log-in and password to enable them to access the online randomization service. Participants will be randomized into the DREAMS trial, in a 1:1 ratio, to 8 mg intravenous dexamethasone or to control (no dexamethasone). A ‘minimization’ procedure using a computer-based algorithm will be used to avoid chance imbalances in important stratification variables. The stratification variables are gender, smoking status, American Society of Anesthesiologists (ASA) score, open and laparoscopic surgical cases, intended postoperative analgesia (intravenous patient-controlled analgesia (PCA), epidural infusion or epidural PCA), and patients within and outside of an ERAS pathway. For trial purposes, ERAS is defined as any recovery process that is expedient over traditional patient care to include but not exclusive to earlier feeding and mobilization. The definition of ERAS is specifically left broad to recognize the differences in implementation of this system across the various units.

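### The primary outcome is a count of vomiting episodes, but the stated 90% power is for two proportions (37% v 28%) of PONV, so power for the defined outcome is not established

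*Protocol article*

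**What the plan says.** Under Primary outcome measure, the protocol article states the objective as to "determine whether preoperative dexamethasone reduces PONV within the first 24 hours". The next sentence defines the variable: "The primary outcome measure will be the number of episodes of vomiting within 24 hours post-surgery, recorded prospectively on trial care charts". As written, this is a count for each patient, and it covers vomiting only.

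Under Power calculation, the trial is sized at 1,350 patients to have "90% power to detect a 24% proportional reduction (37% to 28%) in episodes of PONV". Of that total the article says: "This number includes an additional 10% for crossover and dropout". Allocation is 1:1 (Randomization section).

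The article does not say that the count will be reduced to any versus no vomiting. Nor does it say whether the 37% is a rate of vomiting or of nausea and vomiting together.

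**The concern.** A count per patient has a mean, a rate or a distribution, but it has no 37%. The percentages in the power calculation describe a different variable from the one named as primary. The event differs as well: PONV in one section, vomiting in the other.

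Two things are at stake. First, the 90% cannot be carried over to the outcome as defined. Most patients would have no episodes and a few could have many, so the power of a count analysis depends on the spread of the counts and on the test. Second, the wording leaves room for two primary analyses of the same charts, one of incidence and one of episodes. They can disagree, and the choice between them should not be open once results are known.

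The choice of test and model may properly sit in an analysis plan that is not shown. The type of the primary variable and the event behind the sample size are both stated in the article, and they do not match.

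**Working it through.** **Inputs.** From the article: 37% v 28%, 90% power, 1,350 patients, 10% for crossover and dropout, 1:1 allocation. Assumed: two-sided 5%; the 10% treated as loss of evaluable patients, so 1,350 × 0.9 = 1,215, or 607.5 per arm. The relative reduction is (0.37 − 0.28)/0.37 = 24.3%, in line with the stated 24%.

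**Step 1. Reproduce the stated size as two proportions.** With p̄ = 0.325,

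n per arm = [1.960·√(2p̄(1−p̄)) + 1.282·√(p₁(1−p₁) + p₂(1−p₂))]² / (p₁−p₂)² = 567.1, so 568.

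- Without continuity correction: 1,136 in total; 1,136/0.9 gives 1,263.
- With continuity correction, n′ = (n/4)·[1 + √(1 + 4/(n·0.09))]² gives 590 per arm, 1,180 in total; 1,180/0.9 gives 1,312.
- With an exact 24% reduction (37% to 28.12%) and continuity correction: 606 per arm, 1,212 in total; 1,212/0.9 gives 1,347.

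The last is almost exactly 1,350. Power for 37% v 28% at 607.5 per arm is Φ[(0.09·√607.5 − 1.960·0.662)/0.659] = Φ(1.40) = 91.9%. The calculation is sound, and it is for a binary outcome.

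**Step 2. Power for the count, negative binomial.** The article gives no mean or dispersion, so the dispersion k is varied and the control mean m₁ is set so that 37% of controls vomit at least once: m₁ = (0.63⁻ᵏ − 1)/k, or −ln 0.63 when k = 0. Then

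SE(log ratio) = √[(1/m₁ + k + 1/m₂ + k)/607.5], power = Φ(|ln(m₂/m₁)|/SE − 1.960).

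The reduction can be read in two ways:
- (a) The share vomiting falls from 37% to 28% with the same k in both arms, so m₂ = (0.72⁻ᵏ − 1)/k.
- (b) The mean number of episodes falls in the ratio 28/37 = 0.757.

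| k | m₁ | mean ratio, (a) | power, (a) | power, (b) |
|---|---|---|---|---|
| 0 | 0.46 | 0.71 | 96% | 87% |
| 1 | 0.59 | 0.66 | 98% | 80% |
| 2 | 0.76 | 0.61 | 99% | 73% |
| 3 | 1.00 | 0.56 | >99% | 66% |
| 5 | 1.81 | 0.46 | >99% | 53% |

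Worked row, k = 5 under (b): m₁ = 1.815, m₂ = 1.374, SE = 0.136, |ln 0.757|/SE = 2.05, power = Φ(0.09) = 53%. Rounding the ratio to 0.76 lowers column (b) by about one point.

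**Step 3. Power for the count, other tests.** Simulated counts: 37% v 28% of patients vomit at all, with the same geometric distribution of episodes among those who vomit; 607 per arm; 2,000 replicates.

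| Control mean | t-test on counts | Rank test on counts | Any v none |
|---|---|---|---|
| 0.56 | 79% | 91% | 92% |
| 0.74 | 71% | 90% | 91% |
| 1.00 | 68% | 91% | 92% |
| 1.30 | 64% | 90% | 92% |

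The same outcome on the same patients therefore has power from 53% to over 99%, depending on what the reduction refers to, how dispersed the counts are, and which test is used.

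**The case against.** The strongest reply is that this is loose wording in a condensed article. Episodes are recorded on charts and would naturally be summarised as any versus none; the objective speaks of reducing PONV; and the section on clinical relevance expresses PONV as an incidence (30%, up to 70% in high-risk patients). On that reading the power calculation and the intended analysis agree. It may well be what was meant. But the article does not say so, and the sentence that defines the primary outcome says something else.

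A reader might go further the other way and infer that the trial is underpowered for its primary outcome. The documents do not support that. The low figures come from a t-test on a skewed count or from reading the 24% as a cut in mean episodes. A rank test on the same counts keeps about 90%, and a negative binomial tied to 37% v 28% gives 96% or more. Against that, case (a) needs the mean count to fall by 29% to 54%, which is more than the 24% the article states, so the favourable end also rests on an assumption.

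It is also fair to say that a mean, a dispersion and a named test commonly belong in the full protocol or analysis plan. Their absence here is not the point. What stands is the mismatch between two statements that the article does make.

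**Conclusion.** The point holds in a limited form. The article defines its primary outcome as a count of vomiting episodes and attaches its 90% power to a difference between two proportions, described in terms of PONV. The sample size is right for a binary outcome (about 92% power at 1,215 evaluable patients). For the count as defined, power is not established: about 53% to over 99% across the assumptions tried, with a rank test near 90%. That range rests on assumed means, dispersions and tests, two-sided 5%, and 10% loss. It shows that the stated power does not transfer to the count; it does not show that the trial is too small.

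A second mismatch goes with it. If the 37% came from a source that counted nausea, it is not the control rate for vomiting, and the binary calculation itself would need its rates restated.

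**What to change.** Before unblinding:

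1. Define the primary outcome as the proportion of patients with at least one episode of vomiting within 24 hours of surgery, compared as two proportions, with risk ratio and risk difference and their 95% confidence intervals. Make the number of episodes secondary.
2. State that 37% v 28% refers to any vomiting. If those rates came from PONV including nausea, restate the rates for vomiting and recompute the power.
3. If the trial team prefers to keep the count as primary, state its assumed mean, dispersion and test, and restate the power for that analysis.

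The first option costs a change of wording in the protocol and analysis plan. The same care charts supply both variables, and no more patients are needed provided 37% v 28% stands as the rate of vomiting. At submission 719 of 1,350 patients had been recruited (Trial status), so on the article's figures there was still time to settle this. The third option may need a larger sample: under case (b), 90% power would need about 680 (k = 0) to 1,526 (k = 5) evaluable patients per arm, from n = (1.960 + 1.282)²·(1/m₁ + k + 1/m₂ + k)/(ln 0.757)².
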